#### Compliance

Participants will be considered dropped-out if they do not attend the second and/or third day of intervention.

#### Sample size

The sample size was calculated considering: (1) the two-way analysis of variance (ANOVA); [26] three groups; (3) type I error = 5 % (2-sided); (4) type II error = 20 %; (5) the power of the statistical test = 80 %; and (6) effect size = 20 %. The effect size was obtained considering: (I) the results from the pilot study of Miana et al. [16], which demonstrated a effect of 26 % (pre to post intervention) in the group that received the CV4 technique and (II) Cohen’s *d* which considers 20 % a small effect to calculate sample size and power analysis [27, 28]. Then, it was determined a total of 81 subjects. This calculation was performed in G Power 3 program, version for Mac OS X.

### Side effects

The participants will report every unexpected and unintentional response not related to CV4 technique at every visit.

It is important to establish that this study will not recruit participants suffering from any disease because of the nature of research and the strict exclusion criteria. Regarding CV4 technique, the side effects of cranial manipulation are rare, but described in patients with traumatic brain syndrome [29]. The CV4 technique provides a smooth and gentle manual contact, promoting relaxation and wellness.

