### Intervention

All participants will receive three interventions at the Outpatient Rehabilitation Service of the University Hospital of Brasília (room F49, blue hall), respecting a 7-days washout interval and the same appointment time, which may be scheduled between 8 and 11 a.m.

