### Measurements

#### Primary outcome measurement

The mean change in peak alpha frequency (PAF) will be the primary outcome measure to assess the effects of CV4 technique on nonspecific chronic low back pain. PAF is a measure derived from EEG analysis, and it is defined by two parameters: (1) its occurrence on the frequency axis; and 2) its amplitude on the power density axis. The participants assessment (EEG) and the results statistical analysis will conducted by a blinded researcher ([name]).

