#### Secondary outcome measurement

Secondary outcomes include the mean change in pain intensity (0–10 numeric pain ranting scale) before and immediately after each protocol section. The measurement (pre and post intervention) will be conduced by a researcher blinded to patient allocation ([name]).

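### The article's only side-effect reporting rule, as written, leaves out responses related to CV4

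*Protocol article*

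**What the plan says.** The rule is in the protocol article under Side effects: "The participants will report every unexpected and unintentional response not related to CV4 technique at every visit".

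The same section goes on to say that "the side effects of cranial manipulation are rare, but described in patients with traumatic brain syndrome", and then that "The CV4 technique provides a smooth and gentle manual contact, promoting relaxation and wellness".

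Other sections bear on what would be recorded:

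- Primary outcome measurement: "The mean change in peak alpha frequency (PAF) will be the primary outcome measure".
- Secondary outcome measurement: "Secondary outcomes include the mean change in pain intensity". This is a 0–10 rating taken on either side of each session by a researcher who does not know the allocation.
- Compliance: "Participants will be considered dropped-out if they do not attend the second and/or third day of intervention".
- Intervention: "All participants will receive three interventions", so each participant is exposed to CV4, sham and control.

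**The concern.** A side-effects rule should capture unwanted responses to the treatment under test. This one names CV4 only to exclude what is related to it. Staff who wrote a form from this sentence would ask about responses unrelated to the technique and leave out the related ones.

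Two things are at stake. First, a finding of no CV4-related responses would be built into the collection rule and would carry no information. Second, any comparison of the three conditions would be skewed, because the restriction bears on CV4 alone. This matters for how the trial is to be used: the Discussion says that positive results would support using the technique in a health service for people with chronic low back pain.

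**Working it through.** The article gives no figure on this point, so there is none to reproduce. The check is of the text.

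**Step 1. Break the rule into its conditions.** To be reportable, a response must be (a) unexpected, (b) unintentional and (c) unrelated to CV4. Conditions (a) and (b) are usual for a side-effects section. Condition (c) is the one in question.

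**Step 2. Apply it to the possible cases,** taking (a) and (b) as met.

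| Cause of the response | Unrelated to CV4? | Reportable as written? |
|---|---|---|
| Sham session | Yes | Yes |
| Control session | Yes | Yes |
| Something else, whichever condition came last | Yes | Yes |
| CV4 session | No | No |

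Only the last row drops out, and it is the row that describes harm from the tested technique.

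**Step 3. Look for another route by which that row could be recorded.**

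- The primary outcome is an EEG measure and does not record adverse responses.
- The secondary outcome is pain. It would show pain getting worse straight after a session, in all three conditions, whatever the cause. It would not show other kinds of response, or pain that rises later.
- The Compliance rule defines drop-out by non-attendance and does not mention the reason, so a participant who stayed away because of a reaction is not identified by it.
- The section on participants' protection and ethics covers approval and consent, not event collection.

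No section offsets the rule. The pain rating is the one partial exception.

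**Step 4. Extent.** The Sample size section states "Then, it was determined a total of 81 subjects", and each participant receives all three conditions. The plan is therefore 81 × 3 = 243 sessions, of which 81 (81/243 = one third) are CV4 sessions. The exclusion reaches every planned participant and bears on the effects of that one third of sessions. This is the scope of the rule, not a count of events lost.

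**The case against.** The strongest reply is that this is a slip of language. The sentence stands under a heading on side effects and is followed by remarks on the side effects of cranial manipulation. The writers may have meant any response other than the intended effect of the technique. The article has other language errors, and it condenses a full protocol that is not shown and may collect events properly. That much stands: how events are actually collected is unknown. It does not rescue the sentence. The article states a rule and the rule is wrong as written, so this is not a detail left to another document.

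A reader might also infer more than the text supports:

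- **That the trial can say nothing at all about safety.** This goes too far. The blinded pain rating would show immediate worsening and allows a comparison across conditions, and unrelated responses are still reported.
- **That CV4-related harm is in fact going unrecorded.** The article shows only what the rule says, not what staff do.
- **That participants must judge relatedness themselves.** The sentence says that participants report. It does not say who decides what is related.
- **That the section contradicts itself.** Calling side effects rare and describing them in patients with traumatic brain syndrome sits awkwardly beside the rule. But the Exclusion criteria rule out neurological disease, so the two statements can both hold.
- **That a given number of reactions would be missed.** The article states no rate and calls side effects rare. Any count would rest on an invented rate and would add nothing to a fault in wording.

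It is also fair to say that the trial states no safety objective. That limits the consequence to what may later be said about harm and leaves the EEG and pain analyses untouched.

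**Conclusion.** The point holds as an error in a stated rule, not as a questionable design choice. As written, the article's only adverse-event rule excludes CV4-related responses and keeps those caused by sham and control. If it is followed literally, the trial can make no sound statement on CV4-related harm or on comparative safety beyond the immediate change in pain, and an absence of CV4-related reports could not be read as evidence of safety.

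This rests on two conditions: that the sentence is applied as printed, and that no document outside the article overrides it. If the full protocol already collects all responses, what remains is a published sentence that misstates the rule and still has to be corrected. The size is one of scope (all 81 planned participants). No number of lost events is claimed.

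**What to change.** Delete the five-word qualifier on relatedness from the reporting sentence. State instead that every unexpected or unintended response is recorded at every visit, in all three conditions, regardless of presumed relatedness, and that responses are reported by the condition last received. A response first mentioned on arrival at the second session, for example, would be counted under the condition given at the first.

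If the full protocol already says this, bring the article's sentence into line with it.

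The cost is a one-sentence amendment and matching wording on the case-report form, with no extra visits or staff. It should be made before sessions begin, or as soon as possible if they have begun, because responses not asked about at a visit cannot be reliably recovered later. One limit remains: a rule tied to visits will not pick up a response that arises after a participant's last visit.

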### Participants protection and ethics

The protocol was developed according to the general ethical guidelines, such as Declaration of Helsinki and the new version (2012) of 196/96 resolution of the Brazilian National Health Council (National Research Ethics Committee) for regulatory guidelines for research involving human subjects. This research project and the informed consent were submitted and approved by the Ethics Committee of the Faculty of Health Sciences of University of Brasília. The statement of ethical approval had the code CAAE 27525814.1.0000.0030. For publication of images (Figs. 2 and 3) was obtained the consent of the participant in the first day of experiment.

## Discussion

The aim of the study is to assess the CV4 technique effects on nonspecific chronic low back pain measured by the mean change in the peak alpha frequency (PAF). For this purpose, it was designed a randomized, controlled crossover study with 81 participants.

The investigators hypothesize that CV4 technique can modulate brain cortex electrical activity measured by EEG mean change in the peak alpha frequency. Some studies have investigated CV4 effects on healthy individuals, and there is evidence of changes in the central pain processing – supported by increased power amplitude differences in the alpha band and a shift towards lower frequencies of the dominant peak, measured by resting state EEG; but there is no study on persistent nonspecific low back pain in the current literature.

Therefore, the positive outcomes that can be drawn from this study would support the use of the CV4 technique in designing a sustainable and cost-effective health service for people with chronic low back pain because of the positive effects on functional reorganization human cortex.
